## Abstract

**Background:**

Sub-Saharan Africa (SSA) has one of the highest prevalences of hypertension worldwide. The impact of hypertension is of particular concern in rural SSA, where access to clinics and hospitals is limited. Improvements in the management of people with hypertension in rural SSA could be achieved by sharing diagnosis and care tasks between the clinic and the community. To develop such a community-centred programme we need optimal approaches to identify and risk stratify patients with elevated blood pressure. The aim of the study is to improve the evidence base for diagnosis and risk estimation for a community-centred hypertension programme in two rural settings in SSA.

**Methods:**

We will conduct a cross-sectional study of 1250 adult participants in Kilifi, Kenya and Kiang West, The Gambia. The study has five objectives which will determine the: (1) accuracy of three blood pressure (BP) measurement methods performed by community health workers in identifying people with hypertension in rural SSA, compared to the reference standard method; (2) relationship between systolic BP and cardiovascular risk factors; (3) prevalence of hypertension-mediated organ damage (HMOD); (4) accuracy of innovative point-of-care (POC) technologies to identify patients with HMOD; and (5) cost-effectiveness of different combinations of BP and HMOD measurements for directing hypertension treatment initiation.

**Expected findings:**

This study will determine the accuracy of three methods for community BP measurement and POC technologies for HMOD assessment. Using the optimal methods in this setting it will estimate the prevalence of hypertension and provide the best estimate to date of HMOD prevalence in SSA populations. The cost-effectiveness of decision-making approaches for initiating treatment of hypertension will be modelled. These results will inform the development of a community-centred programme to improve care for hypertensive patients living in rural SSA. Existing community engagement networks will be used to disseminated within the research setting.

## Introduction

Hypertension is the single risk factor that accounts for the highest number of deaths (10.8 million) globally
^
1,
2
^. Sub-Saharan Africa (SSA) has one of the highest estimated prevalences of hypertension worldwide, and in 2019 hypertension was implicated in almost 700,000 deaths in SSA – double the number in 1990
^
1,
2
^. In SSA, hypertension occurs at younger ages, is more severe, remains very poorly controlled, and is more likely to cause complications including heart failure, stroke, kidney disease and premature death than in other regions
^
3,
4
^.

The impact of hypertension is of particular concern in rural SSA where 60% of the region’s 1.1 billion population live. While hypertension prevalence is as high in rural as in urban settings, hypertension awareness, treatment and control is lower in rural settings
^
5–
7
^.

The NIHR Global Research Group on Improving Hypertension Control in Rural Sub-Saharan Africa (
IHCoR-Africa) has been set-up to address these pressing issues and the study described here is part of that effort.

To significantly reduce hypertension-related burden, there is a need to improve the whole hypertension control cascade from awareness (screening and diagnosis) to management (risk stratification and treatment) and control (monitoring, adherence, and referral)
^
8
^. The barriers to effective hypertension management in rural SSA are multiple and complex. At an individual-level, key issues are the asymptomatic nature of hypertension, a lack of understanding of long-term risk, financial impact of taking time away from work to seek treatment, caring responsibilities, and misconceptions about the benefits of pharmocotherapy
^
9–
13
^. At the provider-level
*,* barriers include poor communication between providers and patients, lack of skills and competencies, poor infrastructure, and lack of adequate referral systems for care
^
14
^. Finally, system level
barriers include poor access to health care facilities (caused by overcrowding and long distances between homes and clinics); irregular access to medications; lack of affordable treatments including anti-hypertensive drugs; and underinvestment in health service capacity
^
15
^.

There is growing evidence from other regions where access to medical care is limited that community health workers (CHWs) can play a key role in managing hypertension and its consequences
^
16–
18
^. The HOPE-4 study, conducted in Colombia and Malaysia, showed that a community-centred intervention including screening, diagnosis and treatment with combination pharmacotherapy administered by CHWs and supported by electronic decision support tools improved blood pressure control
^
19
^. Similarly, the COBRA study, in Southeast Asia also showed improved hypertension management delivered using a community-centred intervention by CHWs
^
20
^. This evidence base has led organizations such as the Pan African Society of Cardiology (PASCAR) to advocate for community-centred approaches to improve hypertension management in SSA
^
21
^.

However, equivalent studies in rural SSA are lacking, resulting in limited evidence for clinical recommendations in these settings. Specifically, it is unclear whether recommended approaches to the diagnosis of hypertension and estimation of cardiovascular disease (CVD) risk are appropriate and effective for use in these settings. Clinical guidelines, developed from high-income country studies, ubiquitously incorporate these two aspects when guiding decision making on treatment, including pharmacotherapy
^
22,
23
^. International guidelines recommend repeated clinic-based blood pressure (BP) measurement such as Automated BP Measurement (ABPM)
*,* which can be performed with (attended; aABPM) or without (unattended; uABPM) a health worker present, to mitigate for white coat hypertension. Home Blood Pressure Measurement (HBPM) or 24-hour ambulatory blood pressure monitoring (24-hr ABPM) are also deemed to have a role (
Table 1). However, these international recommendations might not be accurate, feasible or cost-effective in SSA and require further investigation
^
24,
25
^.

**Table 1. T1:** Overview of the methods used to measure blood pressure.

Method	Abbreviation	Brief description
Reference standard		
24-hour Ambulatory BP Measurement	24-hr-ABPM	24-hr-ABPM measures blood pressure on a continuous basis for 24-hours at fixed time intervals. The device will be attached to the body and will be carried by the participant for 24-hours after which the CHWs will transfer data to a study computer.
Alternative methods		
Attended Automated Blood Pressure Measurement	aABPM	CHWs will measure BP using an automated machine in the home of the participant. Measurement procedures will follow international recommendations. CHWs and participants will be blinded to readings until both the aABPM and uABPM measurements are complete.
Unattended Automated Blood Pressure Measurement	uABPM	Using the same BP machine as the aABPM, the participant’s BP will be measured without the CHW present in the room. Once aABPM and uABPM measurements are completed, the CHW will enter the results into study database.
Home BP Measurement	HBPM	The participant receives a digital blood pressure machine at home and is asked to record their blood pressure every morning and evening for 7 consecutive days. CHWs will provide instructions and the device will automatically store readings which CHWs will download at the end of the 7 day period. Literate participants will be asked to write down measurements in supplied diaries.

International guidelines use an absolute risk approach to inform treatment. For example, although all guidelines recommend starting anti-hypertensives for a person with a BP over 160/100 mmHg, the International Society of Hypertension guideline only recommends anti-hypertensives for someone with a BP over 140/90 mmHg, when they are at high CVD risk as determined by risk scoring
^
26
^. In rural SSA, the suitability of existing risk scores is unclear. First, risk scores were developed from populations where the prevalence of known risks such as smoking and high cholesterol is much higher than in rural SSA
^
27–
29
^. Second, compared to high-income countries, most studies in SSA show a substantial burden of hypertension on younger age groups but the age-component of current risk scores classify younger individuals as at minimal risk. This is particularly pertinent given that age-adjusted cardiovascular event rates are higher in low- and middle-income countries than in high-income settings
^
30–
32
^. Third, current risk scores do not consider region-specific factors in SSA, including co-existing chronic communicable disease (HIV and malaria), or exposure to environmental factors (indoor air pollution)
^
33–
35
^. Finally, genetic factors could be contributing to the different epidemiological picture of hypertension and CVD risk in SSA
^
36,
37
^. Therefore, novel approaches to risk estimation are required.

One strong candidate that may have a key role in optimising risk stratification in rural SSA is hypertension-mediated organ damage (HMOD), which includes subclinical damage to organs including the heart, eyes, and kidney among other organs. HMOD has been reported to occur at younger ages and be more prevalent in SSA population
^
38,
39
^. Assessment of HMOD is recommended by clinical guidelines and is strongly associated with CVD among people with hypertension
^
22,
23,
26
^. However, significant challenges persist to measuring HMOD in routine practice, including the clinical resources required for echocardiograms, electrocardiograms, retinal imaging and laboratory blood analysis. Novel point-of-care (POC) diagnostic tools may remove this barrier but have not been validated in this setting.

A key unaddressed challenge is how to embed any new techniques for BP and HMOD measurement within the local health system, especially when CHWs are given more responsibilities without a parallel increase in resources and clinical supervision. To be feasible and sustainable, a community-centred approach to managing hypertension must take account of the health system context.

This paper reports the design of one study that is part of the wider NIHR IHCoR-Africa Group. IHCoR-Africa will also conduct another study addressing the health system challenges and patient experiences will be reported separately. The findings from both studies will contribute to the development of a new community-based intervention for improving hypertension management in rural SSA.

This study has been developed through an equitable collaborative partnership between the London School of Hygiene & Tropical Medicine (LSHTM; UK); the Kemri-Wellcome Trust Research Programme (KWTRP; Kenya) and the MRC Unit the Gambia (MRCG; the Gambia). This partnership was formed during the proposal phase and involved preparatory public and participant involvement and engagement to define the research objectives. Protocol drafting was supported by weekly meetings with representatives from all three partners and included two in person development meetings: November 2022 in Kilifi, Kenya and February 2023 in Fajara, the Gambia. The structure of the partnership enabled all members to have meaningful input in the design of the study.

## Methodology

### Patient and Public Involvement

This study has a strong emphasis on the involvement of the patients and the public. Before protocol development, the study was discussed with community leaders in the study areas so they could suggest changes and discuss how to involve the community. The IHCoR-Africa project has been presented to local departments of health in Kilifi and Gambia, and their recommendations taken into consideration. Throughout the course of the study we will meet with CHWs and patient groups, to understand their experiences as the project is implemented. The collection of data will be mainly performed by CHWs, who are members of the studied communities. After the conclusion of the study, we will involve CHWs and other members of the community in developing an intervention that should improve the detection, treatment, and control of hypertension in rural Gambia and Kenya.

### Study setting

Activities will take place across two rural sites, one in East Africa (
Figure 1). Both settings have a high burden of hypertension, as well as a well-developed research infrastructure to facilitate our work.

**Figure 1. f1:**
[figure not shown]
Map showing location of study sites. West Kiang Health and Demographic Surveillance System (The Gambia) and Kilifi Health and Demographic Surveillance System (Kenya). This figure is an original figure produced by the authors for this article.

Kilifi County is one of the poorest regions in Kenya
^
40
^. The Kilifi Health and Demographic Surveillance System (KHDSS), covers an area of 900 km
^2^ and has a population of around 300,000 people. The prevalence of hypertension is 26% and only 3% of individuals have their blood pressure controlled
^
41
^. Further evidence of the consequences of poor hypertension control is the high incidence of cardiovascular disease in the area, with more than one third of patients admitted with cardiovascular disease dying during their hospital stay
^
31
^.

CHWs deliver health services at the community level and work within a Community Health Unit (CHU), a health service delivery structure within a defined geographical area covering approximately 5,000 people (500–1000 households). CHWs are selected from the community they serve and where possible, are required to have completed secondary education. Each CHU is required to have approximately 10 CHWs.

The Kiang West district in The Gambia covers 750km
^2^ and includes 36 villages with a population of over 14,000 individuals. It is one of the poorest regions in the country with all households in the lowest or low wealth groups. Hypertension prevalence in this region is estimated to be 40%, of whom at least 71% are undiagnosed, and only 4% controlled
^
42
^. The health service delivery in the region is coordinated through the Regional Health Team of the Lower River Region (Mansakonko Administrative Area). The community health nurses (CHNs) deliver services in a defined village cluster within the district. There are 4 CHNs in Kiang West with each handling 7–9 villages. CHNs work with and supervise the village health workers (VHW) who are selected by their communities.

### Study population and sample procedures

We will select an age-stratified random sample of participants aged ≥30 years from the population registers of the Kiang West Health and Demographic Surveillance System (KWHDSS, the Gambia) and Kilifi Health and Demographic Surveillance System (KHDSS, Kenya)
^
43,
44
^. Half of the study population will be selected from The Gambia and half from Kenya. The following age strata will be used: ≥30 to <40, ≥40 to <50, ≥50 - <60, ≥60 - <70 and ≥70y.

Pregnant women will be excluded due to technical difficulties in conducting some of the study measurements such as the echocardiogram and while gestational hypertension remains important it is beyond the scope of our aims and objectives. The participant recruitment approach is shown in
Figure 2.

**Figure 2. f2:**
[figure not shown]
Flow diagram showing participant recruitment, study procedures and objectives.

*Inclusion criteria:*

•   Registered in population registers of the KWHDSS (The Gambia) or KHDSS (Kenya)

•   Aged ≥30 years at the time of enrolment in the study

•   Able to provide written informed consent to participate in the study

*Exclusion criteria*

•   Pregnant women (self-reported)

### Study aim and objectives

We aim to improve the evidence base for diagnosis and risk estimation for a CHW-led community-centred hypertension programme in two rural communities in SSA.

We have the following specific objectives:

1. To determine the accuracy of three alternative blood pressure measurement methods relative to the reference standard and establish the prevalence of hypertension2. To determine the relationship between systolic blood pressure and potential risk factors3. To determine the prevalence of HMOD4. To determine the accuracy of innovative POC technologies to identify patients with HMOD5. To estimate the likely cost-effectiveness of different combinations of blood pressure and HMOD measurements to initiate pharmacological treatment in people with hypertension

### Sample size

The overall sample size for the study is based on the assessment of hypertension prevalence. Assuming a prevalence of hypertension of 25–35%, as detected by the reference standard method (24-hr-ABPM), we will require 832–1003 participants to generate validity parameters for hypertension prevalence with a precision of ±3% overall and ±5% at each of the two sites
^
24,
41
^. We have made a provision for loss of data in 25% of participants due to poor data quality, taking the total number of participants required to 1250, equally divided between Kilifi (N=625) and Kiang West (N=625). This overall sample size will provide sufficient statistical power to address the other aims stated above.

In our assessment of BP and risk factors, and assuming for illustrative purposes that 10% of individuals will have any of the putative factors and that the standard deviation of systolic blood pressure will be 15 mmHg, then 1,003 participants will provide at least 80% statistical power for an alpha of 0.05 to detect a 4mm Hg difference in systolic BP in those with and without the exposure of interest.

Assuming a prevalence of hypertension detected by the reference standard method (24-hr-ABPM) of 30%, we estimate that approximately 300 participants from those recruited in Objective 1 will be classified as hypertensive. With 300 hypertensive patients, we would be able to estimate the confidence interval for a conservative HMOD prevalence of 35% with lower and upper intervals of 29.7% and 40.4% respectively, and that we will have over 95% power for an alpha of 0·05 to test the null hypothesis that the prevalence of HMOD is below 25%. To further explore the difference in the prevalence of HMOD in the hypertensive and general population, we intend to assess all participants recruited into the study for HMOD.

When measured with the reference standard techniques, we expect a 35% prevalence of HMOD among the 300 estimated hypertensive participants and approximately 5% prevalence in the remaining non-hypertensive participants. This will provide us with a total available sample of 153 participants with HMOD. Assuming at least 85% sensitivity of detection of HMOD by the POC strategies we will have at least 80% power for an alpha of 0.05 to test the null hypothesis that the sensitivity is below 75%. As above, we will conduct POC HMOD assessments on all participants.

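### A total of 1,250 with 25% data loss leaves 938 evaluable participants, not the 1,003 (and about 300 hypertensives) on which later sample-size figures rest

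*Protocol article*

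**What the plan says.** All the figures are in the Sample size section of the protocol article.

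- Requirement: "we will require 832–1003 participants to generate validity parameters for hypertension prevalence with a precision of ±3% overall". The target per site is ±5%, and the assumed hypertension prevalence is 25% to 35% on 24-hour ambulatory measurement.
- Loss allowance: "We have made a provision for loss of data in 25% of participants due to poor data quality".
- Total: 1,250 enrolled, 625 from each site.
- Objective 2: for an exposure carried by one person in ten and a systolic SD of 15 mmHg, the section claims: "then 1,003 participants will provide at least 80% statistical power for an alpha of 0.05 to detect a 4mm Hg difference in systolic BP".
- Objective 3: at 30% prevalence, "approximately 300 participants from those recruited in Objective 1 will be classified as hypertensive". The section gives an interval of 29.7% to 40.4% around an HMOD prevalence of 35%, and over 95% power against 25%.
- Objective 4: 35% HMOD in the hypertensives and about 5% in the others are said to give 153 cases, with at least 80% power for a sensitivity of 85% against 75%.

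The section does not say whether the tests are one- or two-sided. It does not limit the 25% loss to any one type of measurement.

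**The concern.** A loss stated as a share of participants has to be applied to the number enrolled. Applied to 1,250, it leaves fewer than the 1,003 that the section goes on to treat as available for analysis. The requirement, the loss rate, the total and the derived counts are all printed, and they do not agree at the upper planning prevalence or in the calculations for the later objectives.

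What is at stake is which precision and power the study can claim if its own loss assumption comes true. The section sizes the whole study on this calculation and says that the result is enough for the other aims, so the evaluable number carries into Objectives 1 to 4.

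**Working it through.** **Inputs** (Sample size section): requirement 832 to 1,003; prevalence 25% to 35%; precision ±3% overall and ±5% per site; loss 25%; total 1,250; 10% exposed, SD 15 mmHg, difference 4 mmHg; HMOD 35% in hypertensives and 5% in others; sensitivity 85% against 75%; alpha 0.05.

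**1. The requirement reproduces.** The plain normal formula 1.96² × p(1−p)/0.03² gives 800 at p = 0.25 and 971 at p = 0.35. A continuity correction raises these to about 833 and 1,004. The exact (Clopper-Pearson) half-width gives 832 and 1,002. The stated 832 to 1,003 is therefore sound.

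**2. The total.**
- 1,003 × 1.25 = 1,254, close to 1,250.
- 1,003/0.75 = 1,337.3, so 1,338 would be needed, 88 more than 1,250.
- 1,250 × 0.75 = 937.5, about 938 (469 per site).
- 1 − 1,003/1,250 = 19.8%, the loss that 1,250 covers for 1,003.

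**3. Precision at 938.** The half-width is 1.96 × √(p(1−p)/938).

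| Prevalence | Normal | Exact |
|---|---|---|
| 25% | ±2.8% | ±2.8% |
| 30% | ±2.9% | ±3.0% |
| 35% | ±3.05% | ±3.1% |

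Per site, the worst case is 1.96 × √(0.2275/469) = ±4.3%, within ±5%.

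**4. Objective 2.** The standard error is 15 × √(1/(0.1N) + 1/(0.9N)), and power is Φ(4/SE − z).

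| N | SE | Two-sided | One-sided |
|---|---|---|---|
| 1,003 | 1.579 | 72% | 81% |
| 938 | 1.633 | 69% | 79% |

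The stated 80% at 1,003 reproduces only with a one-sided test. Two-sided, it takes all 1,250 participants (81%).

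**5. Objective 3.** 0.30 × 1,003 = 301, which matches the stated figure of about 300. 0.30 × 938 = 281. At 281 the normal interval around 35% is 29.4% to 40.6%. Two-sided power against 25% is 95.9% (normal) or 94.7% (exact); one-sided it is about 98%.

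**6. Objective 4, number of cases.**
- Stated 153: reproduces as 0.35 × 300 + 0.05 × 950 = 152.5, where 950 = 1,250 − 300. The hypertensives are counted after loss and the non-hypertensives before it.
- Base 1,003: 0.35 × 300 + 0.05 × 703 = 140.
- Base 938: 0.35 × 281 + 0.05 × 657 = 131.

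Of the 22 cases between 153 and 131, 13 come from the mixed denominator and 9 from the loss allowance.

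**7. Objective 4, power for 85% against 75%.** The normal formula is Φ((0.10√n − z√(0.75 × 0.25))/√(0.85 × 0.15)).

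| Cases | Two-sided, normal / exact | One-sided, normal / exact |
|---|---|---|
| 153 | 86% / 85% | 93% / 93% |
| 140 | 83% / 80% | 91% / 90% |
| 131 | 80% / 76% | 89% / 88% |

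**The case against.** The best defence is that the requirement is a range and that 938 lies inside it. At 30% prevalence, which the section itself uses to count hypertensives, exact ±3% precision needs 928; 928/0.75 = 1,238, which could have been rounded up to 1,250. On that reading the total is correctly inflated for mid-range prevalence. This stands in part: multiplication by 1.25 is the best-fitting explanation but is inferred, and only the upper end of the range conflicts with 25% loss. It does not rescue the later figures, because 1,003 is then used as the analysed number and 300 is 30% of about 1,003.

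A reader might also infer that the loss allowance removes the power for Objectives 2 and 4. The figures do not support that.
- Two-sided power for 4 mmHg is already below 80% at 1,003. The allowance costs about 3 points two-sided and 2 one-sided.
- Most of the drop from 153 HMOD cases is the mixed denominator.
- The null for sensitivity is worded in one direction, and one-sided power at 131 cases is still 88% to 89%.

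Finally, the loss allowance appears in the paragraph on blood pressure prevalence, while HMOD and point-of-care assessments are planned for everyone. If only blood pressure data were lost, HMOD cases could reach 0.35 × 375 + 0.05 × 875 = 175. The text states no such restriction, so 131 follows from its plain reading, but that reading remains an assumption.

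**Conclusion.** The inconsistency is real and its effect is modest. With 25% loss, 1,250 gives 938 evaluable participants and about 281 hypertensives, not 1,003 and 300. To deliver 1,003, the loss must stay at or below about 20%.

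The ±3% target is missed only near 35% prevalence, by 0.05 to 0.1 percentage points. The site target is met, and power for HMOD prevalence stays at about 95% or more. Objective 2 falls to 69% two-sided or 79% one-sided, but the two-sided shortfall mostly predates the loss error. Objective 4 falls to 76% to 80% two-sided, and keeps its stated 80% one-sided.

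The documents do not support a conclusion that the study is too small for its main purpose or that more participants must be recruited. The HMOD figures assume that the 25% applies to all data; the powers depend on a sidedness that the section does not give.

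**What to change.** Keep 1,250 and choose one of two statements:

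- The total allows for about 20% loss. Then 1,003 are evaluable, with about 300 hypertensives and 140 HMOD cases.
- The total allows for 25% loss. Then 938 are evaluable, with 281 hypertensives, 131 HMOD cases and precision of about ±3.1% at 35% prevalence.

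Carry the chosen base through the precision, the hypertensive count, the HMOD count and the powers for Objectives 2 to 4. In either case replace 153, state whether each test is one- or two-sided, and correct the Objective 2 claim to match (72% two-sided or 81% one-sided at 1,003; 69% or 79% at 938). If the 25% is meant for blood pressure data only, say so and give the HMOD base separately.

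The cost is restated figures. No extra recruitment or change in procedures is needed, which matters because the Study status section reports data collection already under way.

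### The 80% power quoted for detecting 4 mmHg with 1,003 participants needs an undeclared one-sided test; a two-sided test gives about 72%, and at the 938 left after 25% data loss neither test reaches 80%

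*Protocol article*

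**What the plan says.** The Sample size section first fixes the overall number from the precision of the hypertension prevalence estimate. That gives 832 to 1,003 participants, raised to 1,250 to allow for a quarter of participants yielding unusable data. The section then says that this number is enough for the other aims.

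For the risk-factor objective (Objective 2) it assumes, as an illustration, that "10% of individuals will have any of the putative factors and that the standard deviation of systolic blood pressure will be 15 mmHg". It concludes: "then 1,003 participants will provide at least 80% statistical power for an alpha of 0.05 to detect a 4mm Hg difference". The difference meant is in systolic BP between exposed and unexposed participants.

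Neither this section nor the summary of statistical analysis says whether the test is one- or two-sided. The analysis summary plans linear and logistic regression of blood pressure and hypertension on the candidate risk factors.

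**The concern.** The sentence gives every input to a two-group power calculation except the sidedness. With the usual two-sided 5% test those inputs do not give 80%. The number analysed is also doubtful, because the section's own allowance for data loss does not leave 1,003 out of 1,250.

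What is at stake is how Objective 2 will be read. With 80% power a true 4 mmHg difference would be missed at most one time in five. At 72% or 69% it would be missed 28% or 31% of the time. A non-significant result for a factor carried by about 10% of participants would then say less about a 4 mmHg effect than the protocol implies.

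**Working it through.** **Inputs, all from the Sample size section.** Analysed N = 1,003; exposed 10%, so 100.3 against 902.7; SD 15 mmHg; difference 4 mmHg; alpha 0.05; enrolled 1,250; data loss 25%. Sidedness is not given, so both versions are computed.

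**Formulas.** SE = SD × √(1/n₁ + 1/n₂). Power ≈ Φ(difference/SE − z), with z = 1.960 two-sided and 1.645 one-sided. Noncentral t values are given alongside as a check.

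**1. The plan's figure, N = 1,003.**
- SE = 15 × √(1/100.3 + 1/902.7) = 1.579; 4/1.579 = 2.534.
- One-sided: Φ(2.534 − 1.645) = Φ(0.889) = 81.3% (noncentral t 81.2%). This reproduces the stated figure.
- Two-sided: Φ(2.534 − 1.960) = Φ(0.574) = 71.7% (noncentral t 71.6%). This does not.

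**2. The number left after loss.**
- 1,250 × 0.75 = 937.5, about 938.
- Retaining 1,003 after a 25% loss would take 1,003/0.75 = 1,338 enrolled. The plan's 1,250 is close to 1,003 × 1.25 = 1,254, which suggests that the allowance was added to the target and not divided out.
- With 1,250 enrolled, 1,003 remain only if the loss is no more than 247/1,250 = 19.8%.

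**3. Power at N = 938 (93.8 against 844.2).**
- SE = 15 × √(1/93.8 + 1/844.2) = 1.633; 4/1.633 = 2.450.
- Two-sided: Φ(0.490) = 68.8% (noncentral t 68.7%).
- One-sided: Φ(0.805) = 79.0% (noncentral t 78.9%).

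**4. What 80% would require.**

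| Quantity | Two-sided | One-sided |
|---|---|---|
| Analysable N for 4 mmHg, 10% exposed (noncentral t) | 1,229 | 968 |
| Power with all 1,250 analysable | 80.7% | 88% |

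The smallest difference detectable with 80% power, two-sided, is (1.960 + 0.842) × SE = 2.80 × SE. That is 4.42 mmHg at 1,003 and 4.57 mmHg at 938. Holding N at 1,003 and the difference at 4 mmHg, two-sided power reaches 80% at an exposure prevalence of about 12.6%, or at an SD of about 13.6 mmHg.

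**5. Do the section's other power statements reveal the convention?** They do not.
- Organ-damage prevalence, 35% against 25% with n = 300: 96.8% two-sided and 98.4% one-sided, against a claim of over 95%.
- Sensitivity, 85% against 75% with n = 153: 86.2% two-sided and 92.9% one-sided, against a claim of at least 80%.

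Both claims hold under either convention.

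**The case against.** **Sidedness is not stated, so the figure cannot simply be called an arithmetic error.** This stands. A reader might infer that the plan's own inputs give 72% and that the stated 80% is miscalculated. The article does not support that, because a one-sided 5% test at 1,003 gives 81%. The two other tests in the same section also have directional null hypotheses, so a one-sided reading is not foreign to it. Against this, the risk-factor sentence is worded without direction: "difference in systolic BP in those with and without the exposure of interest". Objective 2 asks about a relationship, no one-sided test is declared anywhere, and candidate factors such as diet, physical activity and genotype are given no expected direction. Two-sided remains the ordinary reading.

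**The 938 figure is a different matter from the quoted sentence.** This also stands. The sentence speaks of 1,003, and the 938 comes from how the loss allowance was applied. The 25% is an allowance, not a forecast, and a loss below 20% would leave 1,003. The two issues should be kept apart. Both still bear on whether the enrolled number supports the claim.

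**The calculation is illustrative and unadjusted.** The 10% is labelled as illustration, and a modestly more common exposure would restore 80%. Adjustment could help too. If covariates explained 19% of the variance in systolic BP (an assumption; the article gives no figure), the residual SD would be 15 × √0.81 = 13.5 mmHg and two-sided power about 80% at 1,003 and 78% at 938. Correlation between exposure and covariates would work the other way. None of this is in the sentence, whose claim is conditional on the inputs it lists.

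**Nothing in the design depends on it.** This is correct, and it limits the weight of the point. A reader might infer that the study is too small and should enrol more. The article does not support that, because prevalence precision set the overall number.

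**Conclusion.** As written, the power claim for Objective 2 cannot be relied on. Under a two-sided 5% test, power for 4 mmHg at 1,003 is about 72%, some 8 points short. The claim holds at 1,003 only if the test is one-sided, which the article does not say. Two-sided, it holds only if at least 1,229 of the 1,250 (98%) are analysable, which does not fit the section's own loss allowance. At 938 the shortfall is about 11 points two-sided and about one point one-sided.

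These figures assume an unadjusted comparison of means, equal SD of 15 mmHg in both groups, exactly 10% exposed, and data loss unrelated to exposure. The conclusion that 72% is the right headline also rests on reading the undirected contrast as two-sided.

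Severity is moderate. A stated operating figure needs correcting, but it is illustrative, and neither the enrolment target nor the planned analysis depends on it.

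**What to change.** State the sidedness and restate the figure, for example: *With two-sided alpha 0.05, 10% exposed and an SD of 15 mmHg, 1,003 participants give 72% power for a 4 mmHg difference (80% power for about 4.4 mmHg); 938 evaluable participants give 69% (80% power for about 4.6 mmHg), unadjusted.*

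If a one-sided test was intended, declare and justify it, and report 81% at 1,003 and 79% at 938.

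Use the same wording in the statistical analysis plan that the article announces. The cost is one sentence and a slightly less favourable figure. Enrolment, data collection and analysis do not change.
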